## Abstract

**Background**: There is no cure for mitochondrial diseases which manifest in numerous ways including fatigue, muscle weakness, and exercise intolerance. Medical treatment varies and focuses on managing symptoms. Photobiomodulation (PBM) can decrease mitochondrial damage thereby increasing energy production and decreasing cell death. This pilot study will apply PBM to people with mitochondrial encephalomyopathy, lactic acidosis, and stroke-like episodes (MELAS) to examine the safety of application, and if changes occur in symptoms and signs after cross-over application/withdrawal of a sham or active PBM treatment including a two-week period of washout. **Methods**: This study is an exploratory, prospective series N-of-1 (single patient) studies. The protocol is guided by the CONSORT extension for reporting N-of-1 trials (CENT 2015), chosen due to the rarity of mitochondrial diseases, the fluctuating symptomology, and heterogeneity of the clinical presentation. The primary outcome is patient-reported fatigue assessed using the Checklist of Individual Strength and with concomitant evaluation of safety. Secondary measures are of depression, anxiety and stress, sleepiness, physical activity, blood lactate and creatine kinase, physical measures of sit-to-stand, and heel raise capability. Mitochondrial function will be evaluated using hydrogen magnetic resonance spectroscopy for lactate. PBM will be a participant-administered, home-based therapy using a multiple diode flexible array (BeniLight iLED-Pro Multi-Wave Multi-Pulse belt; 465 nm, 660 nm, 850 nm; average irradiance 5.23 mW/cm^2^; total joules: 770.1 J/treatment, all sites; 5 KHz; 20% duty ratio) over the anterior thigh muscles, posterior calf muscles and abdomen for 10 min to each site, three times/week. The safety of the intervention will be assessed. Descriptive statistics, causal analyses of time series data and dynamic modelling will be applied as relevant to the variables collected. Hydrogen magnetic resonance spectra will be acquired and averaged to obtain the content of the targeted hydrogen levels. **Discussion**: The study will provide guidance on whether and how to progress to a larger, randomised cohort study with sham control.

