### 4.3. Intervention

We will assess the clinical response to the application of combined wavelengths of PBM using the BeniLight iLED-Pro Multi-Wave Multi-Pulse PBM device (https://benilight.com/products/benilight-iled-pro, accessed on 21 January 2025) which is an FDA-approved class 2 medical device. The light belt device is 385 mm × 85 mm in size. When programmed in active treatment mode, it emits 465 nm (visible blue), 660 nm (visible red), and 850 nm (infrared invisible) light via LEDs, and a custom lens package with >15° viewing angle; 5.23 mW/cm^2^ irradiance; 5 KHz frequency @20% duty ratio delivering a total fluence/treatment of 770.1 J. During the sham treatment period the LED array of the belt will be disconnected internally from the controller, so all functions display as required but with no output from the device.

The device will be self-applied by participants in the home setting, in contact with the skin over the anterior thigh muscles, posterior calf muscles and abdomen for 10 min at each site. The large quadriceps and gastrocnemius muscles have been chosen as these muscles are most likely to be affected by peripheral fatigue. The abdominal site has been chosen due to our recent (unpublished) findings that abdominally applied PBM has an effect on the gut–brain axis influencing factors associated with central (mental) fatigue.

Depending on the patient’s wishes, the scheduling of the treatment is modifiable, as follows:
‐Six days/week with one day rest each week, alternating each application site (e.g., ten minutes to the abdomen on Monday and Thursday, ten minutes to each thigh on Tuesday and Friday, and ten minutes to each calf on Wednesday and Saturday)

OR

‐Three days/week across all application sites (e.g., Monday, Wednesday, and Friday each week, the device is applied consecutively to the abdomen, the thighs, and calves for ten minutes at each site. The applications can be done in one sitting or spread across the day in separate ten-minute sittings).

The participant choice of application scheduling is permitted to fit in with the participants’ lifestyle but total PBM fluence and irradiance will be equivalent in both schedules.

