MR spectroscopy will be conducted four times as indicated in Figure 1. The MRS scan at time point 2 (after the initial 2-week observational Phase A) will be a baseline measure to establish the participant’s ‘usual’ level of target factors. A second and third MRS scan will be undertaken at the commencement of the active intervention Phase C. The second MRS scan will be taken immediately before the first active PBM treatment. The MRS will be followed by a 10-min PBM treatment of the calf muscles in a room adjacent to the MR scanner. The third MRS scan will be undertaken as soon as possible after the PBM treatment to determine if there is an ‘acute’/immediate change in mitochondrial activity signal following the treatment. After the completion of Phase C, the 8-week at-home self-applied PBM treatment, the final MR spectroscopy will be undertaken to determine if there is a longer-term change/response in mitochondrial activity signal and by how much (reflecting the rationale that light stimulates mitochondrial activity durability and biogenesis).

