### 4.7. Data Management/Analysis

As this is a preliminary series of N-of-1 trials, no power calculations have been performed. A valid sample size for the number of phases to be used in this study cannot be calculated with less than the planned three crossovers since the degrees of freedom for such a test are too small. There is no consensus on the most appropriate statistical method for different N-of-1 designs [36]. Descriptive statistics will be applied as relevant to the variables collected. Causal analyses of the time series data will be examined by graphical representation. Series meta-analysed results may be possible using dynamic modelling to account for unique data characteristics such as time trends and autocorrelation [36]. Due to the statistical challenges posed by N-of-1 trials, measures of pre-post effects may not be possible but these will be explored for the active intervention Phase C.

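### Section 4.3 says the two home schedules give the same total dose, but one treats each site group twice a week and the other three times

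*Protocol article*

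**What the plan says.** Section 4.3 (Intervention) of the protocol article offers two home schedules, to be chosen by the participant.

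- **Six-day schedule:** "Six days/week with one day rest each week, alternating each application site". The worked example gives "ten minutes to the abdomen on Monday and Thursday, ten minutes to each thigh on Tuesday and Friday", and each calf ten minutes on Wednesday and Saturday.
- **Three-day schedule:** on, for example, Monday, Wednesday and Friday, "the device is applied consecutively to the abdomen, the thighs, and calves for ten minutes at each site".

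The section closes by saying that "total PBM fluence and irradiance will be equivalent in both schedules".

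Three other places bear on this. The Abstract gives a single regimen, "for 10 min to each site, three times/week", and an energy figure, "total joules: 770.1 J/treatment, all sites". Section 4.5 describes the treatment between the second and third scans as "a 10-min PBM treatment of the calf muscles in a room adjacent to the MR scanner", which suggests one ten-minute slot for both calves. Section 4.1 says that the treatment parameters are standardised across participants.

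**The concern.** Both schedules use the same device, the same irradiance and ten-minute applications. Total dose then depends only on how many applications are given, and the two worked examples give different numbers. The closing sentence of section 4.3 therefore appears to contradict the schedules just above it. The six-day schedule also misses the weekly frequency in the Abstract.

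At stake is the accuracy of the stated exposure to the only intervention studied. The background section on the proposed role of PBM cites effects that appear to depend on dose and time, and section 5.1 concedes that the dosing choices are theoretical, so the delivered dose needs to be described correctly. Section 4.7 adds that "Series meta-analysed results may be possible using dynamic modelling". With three participants, one different choice of schedule would mix dose with person in any such synthesis or between-participant comparison. Section 6 intends the results to guide the design of further research, and a wrong exposure statement would carry into it.

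**Working it through.** **Inputs**

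- Six-day schedule: three site groups rotated over six days, so 6 / 3 = 2 applications per group per week (section 4.3).
- Three-day schedule: all groups on three days, so 3 applications per group per week (section 4.3).
- Ten minutes per application (section 4.3); 770.1 J per all-site treatment (Abstract); 8 weeks of active treatment (section 4.1).
- Assumption: device output is the same at every placement. Dose is then proportional to device minutes.

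**The plan's figure.** The plan implies a six-day to three-day ratio of 1. It does not reproduce.

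**Abdomen.** This is a single site, so limb timing plays no part.

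- Minutes per week: 2 × 10 = 20 versus 3 × 10 = 30, ratio 0.67.
- Applications over 8 weeks: 2 × 8 = 16 versus 3 × 8 = 24.

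**All sites.** The text does not settle whether ten minutes covers one limb or the pair. A thigh or calf pair therefore takes 10 or 20 minutes per session.

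| Limb timing | Six-day, min/week | Three-day, min/week | Ratio |
|---|---|---|---|
| Per limb in both | 2 × (10+20+20) = 100 | 3 × (10+20+20) = 150 | 0.67 |
| Per pair in both | 2 × (10+10+10) = 60 | 3 × (10+10+10) = 90 | 0.67 |
| Per limb in six-day, per pair in three-day (literal wording) | 100 | 3 × (10+10+10) = 90 | 1.11 |
| Per limb in six-day; in three-day, per limb for one pair only | 100 | 3 × (10+10+20) = 120 | 0.83 |

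All 16 combinations of 10 or 20 minutes for each pair in each schedule span 0.40 (60 versus 150) to 1.11. None gives 1. To see why, let L6 and L3 be the total limb minutes per round, each 20, 30 or 40. Equality needs 2 × (10 + L6) = 3 × (10 + L3), so L6 = 5 + 1.5 × L3. That gives 35, 50 or 65, none of which is a possible value.

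**Per limb.** With per-limb timing in both schedules, each thigh or calf gets 20 versus 30 minutes a week (0.67). On the literal wording it gets 20 versus 15 if the shared slot is split evenly (1.33).

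**Energy, limbs timed alike in both schedules**

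- Per week: 2 × 770.1 = 1,540.2 J versus 3 × 770.1 = 2,310.3 J.
- Over 8 weeks: 12,321.6 J versus 18,482.4 J.

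**Energy, literal wording.** There are 2 × 5 = 10 placements a week versus 3 × 3 = 9.

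- If 770.1 J covers three placements (256.7 J each): 2,567.0 versus 2,310.3 J a week, and 20,536.0 versus 18,482.4 J over 8 weeks.
- If it covers five (154.02 J each): 1,540.2 versus 1,386.2 J a week, and 12,321.6 versus 11,089.4 J over 8 weeks.

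**The case against.** The best defence is that total fluence in the disputed sentence means fluence per treatment. Section 4.3 attaches the word total to the 770.1 J delivered per treatment, and the sentence pairs it with irradiance, which is a device setting. One complete round of all sites could indeed deliver the same energy in either schedule. This does not rescue the text. The sentence is there to assure the reader that the participant's choice leaves exposure unchanged, and a day's treatment in the six-day schedule covers only one site group.

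A second objection is that the weekdays are only examples. Other days would not help: six days shared by three groups in rotation still means two each.

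A third is that the size is uncertain and even reverses direction, and that an 11% gap might loosely pass as equivalent. Part of this stands. The literal reading also strains the energy figure: a six-day round would be 5 × 256.7 = 1,283.5 J, or a three-day treatment 3 × 154.02 = 462.1 J, so 770.1 J could not describe both. The joule figures on that reading are therefore weak, and 0.67 is the better supported ratio. But the 11% net gap hides an abdomen treated one third less and limbs treated one third more.

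A fourth is that the consequence is modest. This stands in part. Comparison of phases within a participant is the core of the design and is not biased. Between-participant confounding arises only if the schedules chosen differ, section 4.7 calls synthesis only a possibility, and section 5.1 disclaims generalisation.

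**Conclusion.** The equivalence statement in section 4.3 is wrong as written. Each site group is treated 2 times a week in one schedule and 3 times in the other. The abdomen's dose ratio is 0.67 on every reading. The overall ratio is 0.67 when limbs are timed the same way in both schedules and 1.11 on the literal wording; other mixed timings give 0.40 to 0.89, and none gives 1. The abdomen ratio and the 0.67 overall ratio need only application counts and equal minutes per application. The joule totals also assume equal output at each placement and that 770.1 J is one full round.

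The point should be corrected, but it does not threaten the within-participant results. If all three participants choose the same schedule, no between-participant confounding arises. The claim would still be false, and under the six-day schedule the Abstract's frequency would not be met.

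**What to change.** First, state whether ten minutes applies to each limb or to the pair, and use that timing in both schedules and in the treatment given between scans. Then take one of these routes:

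- **Two applications per site per week in both:** change the three-day option to two all-site days. The Abstract's frequency would then need correcting.
- **Three applications per site per week in both:** this matches the Abstract. It needs nine site-group sessions a week, so some days of the six-day option would treat more than one group.
- **Leave the schedules unequal:** delete the equivalence claim, record the schedule each participant chose, and report delivered applications and energy per site beside each participant's result.

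The third route is the cheapest: protocol wording, the participant instruction sheet and a line in the results table. The first two also need no extra visits or staff, but they alter the home regimen in a study that already has ethics approval (section 4.6), so the committee may have to be notified.

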In vitro studies of the effects of PBM on mitochondrial activity have utilised various wavelengths (visible and invisible light), irradiances (power output per unit area of treatment), and fluences (photonic energy). Indeed, PBM has been found to increase the activity of respiratory chain complexes in an apparent dose- and time-dependent manner [15]. As defects in any one complex can influence other complexes [8], we propose that PBM may beneficially influence damaged mitochondria in people with MELAS. The best effects of PBM are likely to be in body tissues with increased numbers of mitochondria (such as muscles) using a combination of red, blue, and infrared wavelengths (e.g., [16]).

As pre-conditioning prior to exercise, PBM has moderately strong evidence for increasing the time to exhaustion [17] and low to moderately strong evidence for reducing signs of muscle fatigue in healthy subjects [18] but also in people with chronic obstructive pulmonary disease [19]. PBM significantly reduced muscle fatigue across a range of indicators including reduced ratings of perceived exertion (beneficial effect); increased electromyographic fatigue index (beneficial effect); and increased a range of muscle indicators including peak torque, time to peak torque, total work, average power, and average peak torque (beneficial effects), with significant differences between both PBM and placebo conditions [20]. In that study, when compared to a placebo, PBM applied before exercise improved indicators of muscle performance. A change in absolute deoxyhaemoglobin and myoglobin (deoxy[Hb + Mb]) after a PBM exercise pre-conditioning protocol was suggestive of muscle oxygenation and metabolism changes potentially by increasing local matching of bulk and microvascular oxygen delivery relative to muscle oxygen utilisation [21]. These effects may have been mediated by mitochondrial activity, but the study was not devised to test that effect.

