## 4. Materials and Methods

### 4.1. Study Design

This study is an exploratory, prospective series of N-of-1 studies guided by the CONSORT extension for reporting N-of-1 trials (CENT 2015) [22]. We have chosen this method due to the rarity of MDs, their fluctuating symptomology, and the heterogeneity of clinical presentation. N-of-1 studies test the efficacy of an intervention using one or a small number of patients by sequentially applying and withdrawing the intervention [23]. The simplest of such study designs is an A-B-A design where A is ‘no treatment’ and B is the intervention being studied. Continuous measurement of chosen outcomes occurs through each of the stages.

The PBM parameters will be standardised in all study participants, following an A-B-A-C design (Figure 1) as follows:
‐A = no intervention observational period: Daily patient diary (visual analogue scale; VAS) of fatigue and pain to understand usual (baseline) behaviour of fatigue and pain symptoms, to compare with any change during/after intervention. Fourteen data points will be obtained in each non-intervention period. In this study, the repeated “A” period will also serve as a washout period after the sham phase, to account for any placebo response.‐B = sham intervention period: Daily patient diary (VAS) of fatigue and pain symptoms will be assessed. Fourteen data points will be obtained. We have included a sham phase in this series of N-of-1 trials to satisfy the requirement to understand if there may be a placebo element to the initial application of light. To reduce the burden on participants, we have chosen a 2-week sham period which is expected to demonstrate any change from baseline. The following A phase will assist in determining the durability of any placebo effect that we may need to consider in a future study.‐C = active intervention (PBM application) period: Twice-weekly patient diary of fatigue and pain symptoms will be assessed. Sixteen data points will be obtained over an 8-week period of treatment. The intervention period is based on exercise science findings demonstrating increased mitochondrial activity with endurance exercise [24] and mitochondrial biogenesis after 4–6 weeks of interval training in healthy individuals [24,25]. If PBM influences muscle mitochondrial function, we expect that 8 weeks of home-based intervention may be required to demonstrate effects in a clinical population that would normally struggle to participate in exercise programs.

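### The two permitted home schedules do not deliver the same total fluence: as written, the six-day option gives each site two ten-minute sessions a week and the three-day option gives three

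*Protocol article*

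**What the plan says.** Section 4.3 (Intervention) offers two schedules, and the participant chooses.

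- **Six-day schedule:** "Six days/week with one day rest each week, alternating each application site". The example gives "ten minutes to the abdomen on Monday and Thursday, ten minutes to each thigh on Tuesday and Friday", with each calf on Wednesday and Saturday.
- **Three-day schedule:** on each of three days, "the device is applied consecutively to the abdomen, the thighs, and calves for ten minutes at each site".

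The section then says that "total PBM fluence and irradiance will be equivalent in both schedules". It gives one irradiance (5.23 mW/cm²) and one session length (ten minutes per site). It mentions no longer session, higher output or extra weeks for either schedule.

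Two other statements bear on the dose. The Abstract sets treatment "for 10 min to each site, three times/week". Section 4.1 (Study Design) says "The PBM parameters will be standardised in all study participants".

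**The concern.** If session length and irradiance are fixed, cumulative fluence at a site depends only on how many sessions that site receives. The two schedules give different counts, so they cannot deliver equal totals. Only the three-day schedule meets the frequency given in the Abstract.

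There are three participants and each picks a schedule. If their choices differ, dose is completely confounded with participant. The article's own rationale holds that dose matters: "PBM has been found to increase the activity of respiratory chain complexes in an apparent dose- and time-dependent manner". A weaker change in the Checklist of Individual Strength (CIS), or in the end-of-Phase-C spectroscopy scan, in a six-day participant could not be told apart from a lower dose. Any combined analysis of the series (Section 4.7), and the design of further research (Section 6), would treat unequal exposures as equal because the protocol says they are.

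**Working it through.** **Inputs**

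- Six-day schedule: 6 treatment days a week, 3 site groups (abdomen, thighs, calves), one group per day in the printed example (Section 4.3).
- Three-day schedule: 3 treatment days a week, all sites each day (Section 4.3).
- Session length 10 min = 600 s per site; irradiance 5.23 mW/cm² = 0.00523 W/cm² (Section 4.3).
- Energy for one treatment of all sites: 770.1 J (Abstract and Section 4.3).
- Phase C: 8 weeks; sham Phase B: 2 weeks (Section 4.1).

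**The plan's own figure.** The equivalence statement implies a six-day to three-day ratio of 1.0 for total fluence. The count below does not reproduce it.

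**Sessions per site per week**

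- Six-day: 6 days / 3 groups = 2. With one group per day, this holds whichever weekdays are used.
- Three-day: 3.
- Ratio: 2/3 = 0.667, so the shortfall is 1 − 2/3 = 33.3%.

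**Dose per site**

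Radiant exposure per session = 0.00523 × 600 = 3.138 J/cm².

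| Per site | Six-day | Three-day |
|---|---|---|
| Minutes per week | 2 × 10 = 20 | 3 × 10 = 30 |
| Sessions in Phase C | 2 × 8 = 16 | 3 × 8 = 24 |
| Minutes in Phase C | 160 | 240 |
| J/cm² per week | 2 × 3.138 = 6.28 | 3 × 3.138 = 9.41 |
| J/cm² in Phase C | 50.2 | 75.3 |

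**Energy over all sites, taking 770.1 J per full round as given**

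- Per week: 770.1 × 2 = 1,540.2 J versus 770.1 × 3 = 2,310.3 J.
- Over Phase C: 12,321.6 J versus 18,482.4 J.

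How 770.1 J was derived does not matter here. The belt outline (38.5 × 8.5 = 327.25 cm²) would give 0.00523 × 327.25 × 600 = 1,026.9 J for a single placement, so the emitting area behind the stated figure is not given. It cancels from the 2:3 ratio.

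**Sensitivity to placements.** The article does not say how many belt placements a pair of limbs needs. Total belt-minutes per week:

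| Reading | Six-day | Three-day | Ratio |
|---|---|---|---|
| Each limb separate in both (5 placements) | 5 × 10 × 2 = 100 | 5 × 10 × 3 = 150 | 0.67 |
| Each pair one placement in both (3 placements) | 3 × 10 × 2 = 60 | 3 × 10 × 3 = 90 | 0.67 |
| Limbs separate in six-day, paired in three-day | 100 | 90 | 1.11 |

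None gives equality. The abdomen gets 20 versus 30 minutes in every row.

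**Sham phase.** If the same schedules are used in Phase B, each site gets 4 versus 6 sham sessions over two weeks.

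**The case against.** **Limb placement.** The six-day text speaks of each thigh and each calf; the three-day text speaks of thighs and calves with ten minutes per site. If a pair shares one placement only in the three-day option, total belt time is 11% higher on the six-day schedule. If that placement is split equally between the two limbs, each limb gets 3 × 0.5 = 1.5 belt-sessions a week against 2, so the six-day limb gets a third more. This point stands: the size and direction for the limbs depend on an unstated detail. It does not rescue the equivalence statement.

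**The days are only an example.** One site group per day appears only inside the example; the rule itself asks only for alternation, and a pattern with three sessions per site could satisfy it. That is fair, but the example is the only pattern printed and the one a participant would follow. It contradicts the sentence placed beside it.

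**Total fluence might mean per treatment.** Section 4.3 does use the term that way for the 770.1 J, and one complete round of sites is equal in both schedules. But the disputed sentence compares schedules, and one completes two rounds a week while the other completes three. The mismatch with the Abstract remains on either reading.

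**Standardised parameters** in Section 4.1 may mean device settings only. This is plausible, so that inconsistency is the weaker one, and the finding does not need it.

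**Consequences are limited.** Each participant is their own control, the before-and-after scan pair at the start of Phase C follows one fixed calf treatment, pooling is only tentative, and Section 5.1 admits that dosing is theoretical. The dose-dependence cited comes from in vitro work, and nothing in the article shows that a one-third difference matters clinically. All of this limits the severity. It does not make the dose statement correct, and a pilot that informs a larger study needs to know what dose was given.

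**Conclusion.** The equivalence statement is wrong for total fluence as the schedules are printed. The six-day option gives 20 rather than 30 minutes per site per week and 16 rather than 24 sessions over Phase C, one third less. It also falls short of the Abstract's three sessions per site.

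This size assumes one site group per day, as in the example, and the same placement of paired limbs in both schedules. Without the second assumption the limb comparison is uncertain in direction. The abdominal shortfall of one third does not depend on it.

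The error should be corrected, but it does not invalidate the trial. Between-participant confounding arises only if participants choose different schedules, which the protocol allows. If all three chose the six-day option, doses would match each other but not the Abstract.

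**What to change.** Keep the participant's choice and equalise the dose.

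- **Preferred:** on the six-day schedule, treat abdomen and thighs on Monday, Wednesday and Friday and calves on Tuesday, Thursday and Saturday. Each site then gets 3 × 10 = 30 minutes a week with session length unchanged. With 770.1 J per round, both schedules deliver 2,310.3 J a week and 18,482.4 J over Phase C.
- **Second choice:** keep one site group per day and use 15-minute sessions (2 × 15 = 30 minutes). This raises exposure per session from 3.138 to 0.00523 × 900 = 4.707 J/cm² and departs from the ten-minute session, which is less attractive in a study that also assesses safety.

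In either case, state whether each thigh and each calf has its own ten-minute placement, use the same pattern in sham Phase B, and record the schedule chosen and the sessions completed per site.

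If two sessions per site is what the six-day option intends, remove the equivalence sentence, correct the Abstract and report delivered dose for each participant.

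The cost is a wording change in Section 4.3 and in the participant instructions. Under the preferred fix, a six-day participant adds 90 − 60 = 30 belt-minutes a week with three placements, or 150 − 100 = 50 with five.
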